### Statistical analysis

For this study, MEP data will be processed and analyzed statistically using the Statistical Package for the Social Sciences (SPSS, version 26.0). For normally distributed continuous data, repeated-measures analysis of variance will be used for intra-group comparisons and independent-samples *t*-test for inter-group comparisons; for non-normal data, Friedman test and Wilcoxon rank-sum test will be adopted; for count data, Pearson χ^2^ test will be employed. The intraclass correlation coefficient (ICC) will be used to assess the inter-rater reliability of MEPs and MAS (17), and Cronbach's α coefficient will be used to test the internal consistency of scales. A *p* value < 0.05 will be considered statistically significant. The measurement of MEPs will follow the guidelines of the International Federation of Clinical Neurophysiology (27), and the FMA-UE will refer to the criteria for clinically important differences (22). To investigate the therapeutic mechanism, we will examine the association between changes in neurophysiological measures and improvements in clinical behavioral outcomes. Specifically, we will calculate the change scores (from baseline to post-intervention) for each participant in MEP amplitude (or cortical silent period) and in the Fugl-Meyer Assessment for Upper Extremity (FMA-UE) scores. We will then use Spearman correlation analysis to determine whether a significant correlation exists between these two change scores. We hypothesize that participants with greater clinical improvement will also exhibit more pronounced beneficial changes in corticospinal excitability.

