**Anticipated results:**

We hypothesize that Group 3 (combined stimulation) will yield the greatest reduction in spasticity (MAS decrease ≥ 1) and the most significant improvements in upper-limb function (FMA-UE, ARAT) compared to Groups 1 and 2. These clinical gains are expected to correlate with neurophysiological changes (MEP amplitude, cortical silent period), supporting the central-peripheral synergy model.

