### Sample size estimation

As the differential effects of priming iTBS on hemiparetic upper-limb training have yet to be examined, we based our sample-size estimate on existing three-group trials. A recent meta-analysis reported a pooled Cohen's *d* = 0.60 favoring iTBS for upper-limb motor improvement. For a three-group design, this translates to an effect size *f* of ~0.30 (15). *A priori* power analysis (power = 0.80, two-tailed α = 0.05) indicated that 45 participants would be required. Accounting for an anticipated 15% dropout rate, we will recruit 18 participants per group, for a total sample size of 54. This recruitment target is expected to yield at least 45 participants completing the trial.

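### The only analysis that spans the visits is confined to within-group comparisons, and the between-group tests name no group-by-time term, no baseline covariate and no outcome scale (post or change)

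*Protocol article*

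**What the plan says.** All of the planned testing is in one paragraph of the protocol article, under Statistical analysis.

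- **Continuous, normally distributed data:** "repeated-measures analysis of variance will be used for intra-group comparisons and independent-samples" t-tests for inter-group comparisons.
- **Continuous, non-normal data:** "Friedman test and Wilcoxon rank-sum test will be adopted". By analogy, Friedman is the within-group test and rank-sum the between-group test.
- **Count data:** Pearson chi-squared.
- **Threshold:** a p "value < 0.05 will be considered statistically significant".
- **Change scores:** these appear once, for the mechanistic correlation: "we will calculate the change scores (from baseline to post-intervention) for each participant in MEP amplitude (or cortical silent period") and in FMA-UE. They are not mentioned for the comparison of arms.
- **Scope:** the paragraph opens with "MEP data will be processed and analyzed statistically using the Statistical Package for the Social Sciences", then goes on to MAS reliability, the scales and FMA-UE. No other efficacy analysis is given.

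The hypothesis is in the Abstract, Anticipated results: "We hypothesize that Group 3 (combined stimulation) will yield the greatest reduction in spasticity", and the most improvement in FMA-UE and ARAT, compared with Groups 1 and 2. Table 1 schedules MEPs, MAS, FMA-UE, ARAT and the Modified Barthel Index at baseline (T0), post-intervention (T1) and 2-week follow-up (T2).

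**The concern.** The hypothesis concerns a difference between arms in how much they change. Repeated-measures ANOVA is the natural place for a group-by-time term, but the plan restricts it to each arm separately, where there is no group factor. What remains for the hypothesis is a two-sample test on a quantity that the plan does not define.

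Two things are at stake.

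1. **Interpretation.** Three separate within-arm p-values invite the conclusion that an arm which crosses 0.05 worked and one which does not failed. The design makes this more likely to mislead. Every arm receives active stimulation at one site or both plus 30 minutes of conventional therapy per session, and there is no all-sham arm. Improvement within an arm therefore mixes stimulation, therapy and recovery.
2. **Precision.** Baseline values are collected for every outcome. Leaving them out of the between-group test, or using them only by subtraction, gives up power that costs no patients or visits.

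**Working it through.** The analysis paragraph gives no figure to reproduce, so the check sets the tests against the hypothesis and then sizes the consequences.

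**Inputs from the Sample size estimation section:** d = 0.60; two-tailed alpha 0.05; 45 expected completers, so 45/3 = 15 per arm; 54 recruited, so 54/3 = 18 per arm.

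**Assumptions, because the article gives no figure:** the correlation rho between baseline and outcome (0.5, 0.7, 0.8, with 0.3 as a low case); within-arm power of 50%, 80% or 90%; d expressed in SDs of the raw score, with equal SD at both times.

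**Step 1: which planned test addresses the hypothesis?**
- Within-arm repeated-measures ANOVA or Friedman tests whether one arm changes over time. It contains no comparison of arms.
- A two-sample test on post scores compares arms but makes no use of baseline.
- A two-sample test on change scores is a pairwise group-by-time contrast for one visit.

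Only the last two bear on the hypothesis, and the article does not say which is meant.

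**Step 2: how often would within-arm p-values mislead?** Suppose all arms improve equally and each within-arm test has power p. With independent arms, the probability that Group 3 is significant while at least one other arm is not is p × (1 − p²).
- p = 0.50: 0.50 × (1 − 0.25) = 0.375
- p = 0.80: 0.80 × (1 − 0.64) = 0.288
- p = 0.90: 0.90 × (1 − 0.81) = 0.171

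**Step 3: precision of one between-arm contrast.** With the raw-score SD set to 1, the SD of the analysed quantity is:
- post score: 1
- change score: √(2(1 − rho))
- baseline-adjusted (ANCOVA): √(1 − rho²)

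The effective standardised difference is 0.60 divided by that SD. Power comes from the noncentral t distribution with 2n − 2 degrees of freedom and noncentrality (effective d) × √(n/2). The one degree of freedom spent on the covariate is ignored; it changes power by about 0.1 percentage point.

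At 15 per arm:

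| rho | Post score | Change: SD, effective d, power | ANCOVA: SD, effective d, power |
|---|---|---|---|
| 0.3 | 35% | 1.183, 0.507, 27% | 0.954, 0.629, 38% |
| 0.5 | 35% | 1.000, 0.600, 35% | 0.866, 0.693, 45% |
| 0.7 | 35% | 0.775, 0.775, 54% | 0.714, 0.840, 60% |
| 0.8 | 35% | 0.632, 0.949, 71% | 0.600, 1.000, 75% |

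For rho of 0.5, 0.7 and 0.8, adjustment gains about 9, 25 and 40 percentage points over a post-score test, but only about 9, 7 and 4 over a change-score test.

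As detectable differences at 80% power, the post-score test needs 1.06 SD. A change-score test needs 1.06, 0.82 and 0.67 SD, and ANCOVA 0.92, 0.76 and 0.64 SD.

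At 18 per arm the post-score test has 42% power and ANCOVA 52%, 69% and 83%.

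**The case against.** Several counter-arguments have force.

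- **Pairwise tests in a three-arm trial are not wrong.** The claim that Group 3 beats Groups 1 and 2 is two pairwise contrasts, and a two-sample comparison of randomised arms keeps its error rate for each contrast. This stands. The fit between the three-group f and the planned tests is a sample-size matter and is not argued here.
- **The plan may intend change scores.** The hypothesis and the MAS benchmark are both worded as decreases. If so, the between-group tests do use baseline, and the gain from adjustment is the smaller one shown above. A reader might infer that the plan discards baseline information. The article does not say so; it leaves the quantity open.
- **The plan does not say that it will infer superiority from within-arm significance.** It plans inter-group tests separately. This is right: the percentages in Step 2 describe an invitation to misread, not a stated decision rule.
- **Chi-squared on responders** (MAS decrease of at least 1) could compare all three arms on a baseline-referenced outcome. The article does not make that link.
- **Dropout.** A reader might infer that repeated-measures ANOVA forces a complete-case efficacy analysis. It is planned only within groups, so its deletion of incomplete cases does not govern the between-group tests, and missing-data handling may be in a fuller document that is not shown.
- **Scope.** The paragraph opens with MEP data. Applying it to the clinical outcomes is an inference, made because no other efficacy analysis is given.

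Covariates are often left to an analysis plan. Here, however, the article names the tests and assigns each a role, so the choice is stated, not merely left out.

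**Conclusion.** The point holds in a limited form. As written, the only analysis that spans the visits cannot test the hypothesis. The tests that can are left without a defined quantity, and no baseline adjustment is named. The between-arm tests are valid; the loss is one of clarity and precision.

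The size of the loss depends on what the t-tests were meant to compare and on an unknown correlation. At 15 per arm it is 9 to 40 percentage points of power for rho of 0.5 to 0.8 if post scores are meant, and 4 to 9 if change scores are meant. The figures rest on d = 0.60 being in raw-score SDs, a scale that the article does not give. If it is instead in change-score SDs, adjustment raises 35% to 45%, 41% and 39% at rho of 0.5, 0.7 and 0.8.

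This should be fixed before analysis. A stronger reading, that the efficacy comparison is invalid, is not supported.

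**What to change.** Rewrite the efficacy part of the Statistical analysis section as follows.

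1. For FMA-UE, ARAT, Modified Barthel Index and MEP measures, use a baseline-adjusted linear model: ANCOVA at T1, or a mixed model of T1 and T2 values with baseline value, group, visit and group-by-visit. Include all randomised participants with at least one post-baseline value (for ANCOVA, a T1 value). Anyone lost before T1 with no later value contributes nothing to either model, and the text should say so.
2. Report Group 3 minus Group 1 and Group 3 minus Group 2 at T1, each with a 95% CI.
3. For MAS, which has six ordered grades, use an ordinal model with baseline MAS as covariate.
4. Make within-group changes descriptive, without p-values.
5. State that these methods apply to the clinical outcomes as well as to MEPs.

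The cost is a change of wording and slightly more analysis work. The SPSS package already named can fit these models, and no extra data are needed. The one new burden is the proportional-odds assumption for MAS, which has to be checked and is hard to assess at 15 to 18 per arm.

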Building on this framework, we designed an RCT to formally test these mechanisms and establish clinical feasibility. This protocol makes three contributions: (1) a standardized PMT titration method, (2) first RCT testing the W-shaped model through dual-site pTBS, and (3) a rigorous sham-controlled design. Primary objectives are to evaluate pTBS effects on spasticity/function, investigate neurophysiological mechanisms, and establish safety profiles. Secondary objectives include validating central-peripheral synergy, comparing single vs. dual-site stimulation, and generating effect sizes for future trials.

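### The observed distribution chooses between mean-based and rank-based tests at 15 to 18 per arm, and no effect estimate is named although effect sizes are an objective

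*Protocol article*

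**What the plan says.** The Statistical analysis section sets a two-way rule. On one side: "For normally distributed continuous data, repeated-measures analysis of variance will be used for intra-group comparisons", with independent-samples t-tests between groups. On the other: "for non-normal data, Friedman test and Wilcoxon rank-sum test will be adopted". Counts go to a chi-square test. No outcome is assigned to either side, and the article does not say how normality is judged or whether that is done per outcome, per arm or per visit. The criterion for a result is that a *p* "value < 0.05 will be considered statistically significant". Neither side names an estimate or a confidence interval. The one reference to magnitude is that FMA-UE will be read against published criteria for a clinically important difference.

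Two other places matter. The Introduction includes "generating effect sizes for future trials" among the secondary objectives. Sample size estimation gives 54 recruited and 45 expected to complete, in three equal arms.

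**The concern.** A t-test compares means. A rank-sum test asks how often a participant in one arm scores above a participant in the other. If the sample's shape decides which is used, the question answered for an outcome is settled only after the data are seen. It can then differ between the post-intervention visit (T1) and the 2-week follow-up (T2), or between one pair of arms and another. With 15 to 18 per arm, a normality check has little power to detect real skewness, and it flags truly normal data at its own error rate.

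This matters for MAS in particular, because the Outcome measures section counts a sustained drop of at least one point as meaningful, so T1 and T2 results have to be read together. It also matters for the effect-size objective. A future trial needs one defined quantity per outcome with its uncertainty, and a p-value threshold supplies neither.

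**Working it through.** **Arm sizes (Sample size estimation).** 54 / 3 = 18 recruited per arm; 45 / 3 = 15 completing. The dropout step reproduces: 45 / 0.85 = 52.9, rounded up to 54 for equal arms, and 54 × 0.85 = 45.9. Whether 45 follows from the stated effect size is a separate matter and is not used here.

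**How often the gate switches normal data.** The planned between-group tests are two-sample, so two arms are checked. With a 5% normality test in each arm, the chance that at least one fails is 1 − 0.95² = 9.75%.

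**How often T1 and T2 differ.** Assumptions, none stated in the article: Shapiro-Wilk at 5% in each arm at each visit; t-test only if both arms pass, otherwise rank-sum; correlation 0.7 between T1 and T2; gamma-shaped margins for skewed data. Results from 4,000 simulated comparisons per row:

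| n per arm | Skewness | Sent to ranks | T1 and T2 differ | Type I error, gated | Type I error, always t-test |
|---|---|---|---|---|---|
| 15 | 0 | 9.8% | 16.5% | 5.3% | 5.3% |
| 15 | 0.7 | 24.5% | 32.4% | 5.0% | 4.7% |
| 15 | 1.0 | 38.6% | 40.2% | 4.9% | 4.5% |
| 18 | 0 | 10.1% | 17.0% | 5.1% | 4.8% |
| 18 | 0.7 | 27.6% | 34.2% | 5.6% | 5.2% |
| 18 | 1.0 | 45.7% | 42.2% | 5.1% | 4.5% |

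Other runs on the skewed settings gave 34 to 43% disagreement, so these figures are good to about two points. Another set of 3,000 runs per setting put type I error at 4.3 to 6.6% gated and 4.2 to 6.1% for an always-t-test.

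**MAS.** With an assumed spread over the six grades, 70% (n = 15) to 78% (n = 18) of raw-score comparisons went to ranks, and T1 and T2 differed in 39% and 33%. With an assumed distribution of change scores, 96 to 97% went to ranks and the visits differed in only 5 to 7%.

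**What a fixed, baseline-adjusted model would add.** Inputs from Sample size estimation: d = 0.60 ("pooled Cohen's *d* = 0.60 favoring iTBS for upper-limb motor improvement"), two-tailed alpha 0.05, 18 per arm. The baseline correlation ρ is assumed to be 0.5 to 0.8.

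- Unadjusted t-test: noncentrality 0.6 × √(18/2) = 1.80 on 34 df; power 0.42.
- Adjusted: effective d = 0.6 / √(1 − ρ²). For ρ = 0.5 this is 0.6 / 0.866 = 0.693; for ρ = 0.8 it is 0.6 / 0.6 = 1.00. On 33 df, power is 0.52 and 0.83.
- Chance baseline imbalance inflates the variance by about 1 + 1/(36 − 4) = 1.031, which brings these to about 0.51 and 0.82.

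**The case against.** The article names no normality test and no unit of decision. It can be read as one decision per outcome, in which case T1 and T2 never differ, and an unseen analysis plan may say so. That stands, and it makes the disagreement rates conditional. It does not remove the point: even one decision per outcome is taken from the trial data, and a plan that follows the article inherits the rule.

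The gate also does no visible inferential damage: type I error stays close to that of an always-t-test. This stands in full.

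A reader might infer three stronger things that the document does not support.

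- *That the effect-size objective fails because MAS goes to rank tests.* The article does not assign MAS to a branch. A scale that always went to ranks would be tested consistently, and the probability of superiority is U/(n₁n₂), taken directly from the rank-sum statistic. The t-test branch names no estimate either, so the gap is not caused by the rank path.
- *That the check spans all three arms*, giving 1 − 0.95³ = 14.3% for normal data. The planned between-group tests compare two arms.
- *That MEP change should be analysed as a log ratio.* Any advantage rests on assumed noise figures, and the ratio is undefined when a response is absent. The eligibility criteria require no recordable MEP, and the Discussion itself asks whether patients without MEPs can benefit.

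**Conclusion.** The point holds as a matter of consistency and reporting. The article fixes a rule under which the data choose the test, and it names only a significance threshold despite an objective that needs estimates. If normality is judged per arm and visit, T1 and T2 would be tested differently in about 17% of comparisons with normal data and 34 to 43% with skewness 0.7 to 1.0. Those rates rest on the assumed Shapiro-Wilk check, two arms and a between-visit correlation of 0.7; they fall to zero if one decision is made per outcome.

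A reader might conclude that the p-values are invalid. The simulations do not show that. What is at risk is a mixture of estimands across visits and results without an effect size or interval. This should be changed before the analysis but does not undermine the trial.

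**What to change.** Remove the normality gate and name one method per outcome in advance.

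- **FMA-UE, ARAT, Modified Barthel Index, RMT and latency:** a linear model adjusted for the T0 value, reporting the adjusted mean difference between arms with a 95% CI at each visit.
- **MAS:** one ordinal method at both T1 and T2, either a proportional-odds model with its odds ratio or the rank-sum test with the probability of superiority, with a 95% CI.
- **MEP amplitude:** likewise one named method, with a statement of how absent responses are handled.
- **Rank or bootstrap versions:** sensitivity analyses only.

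Different tests at T1 and T2 then cannot occur. The cost is analysis wording; no extra participants, visits or measurements are needed, since T0 values are already collected. The downside is reliance on model assumptions, which the sensitivity analyses address. The gain in pairwise power, from about 0.42 to between 0.51 and 0.82 at 18 per arm and d = 0.6, depends on the assumed baseline correlation of 0.5 to 0.8.

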## Methods

### Study design

The study is a prospective, single-center, randomized, parallel-controlled design. Fifty-four patients will be randomly assigned to one of three groups (Figure 1): (1) active iTBS+sham cTBS; (2) sham iTBS+active cTBS; (3) active iTBS+active cTBS in 1:1:1 ratio. The trial comprises three phases (Table 1): baseline assessment, post-training assessment (i.e., after 10 sessions) and follow-up assessment (i.e., 2 weeks after the completion of all training sessions). Intervention will be conducted five sessions a week, with a total of 10 sessions. All participants will sign an informed consent form. Adverse reactions will be handled in accordance with the preset protocol. The whole study will be performed at the Department of Rehabilitation Medicine of South China Hospital of Shenzhen University (Shenzhen, Guangdong Province, China). The results will be published in peer-reviewed journals and reported at academic conferences. The protocol is registered with Chinese Clinical Trial Registry (Registration No. ChiCTR2500105190). The trial will be conducted in accordance with the Consolidated Standards of Reporting Trials (CONSORT) guidelines, and the study protocol has been approved by the Institutional Review Board of Ethics Committee of South China Hospital of Shenzhen University (grant no. HNL.S2025041).

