### Outcome measures

MEPs are compound muscle action potentials recorded from a target muscle after a single-pulse TMS over the primary motor cortex; they provide an objective index of corticospinal excitability and conduction integrity, with excellent test-retest reliability [Intraclass Correlation Coefficient (ICC) = 0.75–0.94, Kendall's tau = 0.81] (17). In this trial, MEPs will be used to quantify corticospinal plasticity before and after the intervention.

Although the pTBS intervention targets the forearm muscles (FCR and ECRL), MEPs were recorded from the abductor pollicis brevis (APB) because it is a standard target muscle in TMS studies, recommended for its consistent and robust MEP responses and well-defined cortical representation in the primary motor cortex (M1) hand area (17). This approach provides a reliable and comparable measure of overall corticospinal excitability.

Briefly, Ag/AgCl surface electrodes will be placed over the abductor pollicis brevis of the paretic limb. A Magstim 200^2^ stimulator with a 70-mm figure-of-eight coil will deliver 0.2-Hz stimuli to the affected-hemisphere M1 hand area while the participant rests. The following metrics will be obtained: (1) resting motor threshold (RMT), defined as the lowest stimulus intensity eliciting ≥ 50 μV MEPs in ≥ 5 of 10 consecutive trials (17); (2) MEP peak-to-peak amplitude (mV) measured at 120%RMT, averaged across 10 artifact-free trials, as a marker of corticospinal excitability; and (3) MEP latency (ms) from stimulus artifact to onset of the first deflection, reflecting central conduction time. All measurements will be performed by the same assessor at baseline, immediately post-intervention, and at the 2-week follow-up to ensure consistency.

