Positive results remain contingent on three unresolved conditions: (1) Technical—can the dual-coil apparatus be miniaturized into a wearable? (2) Physiological—does efficacy depend on residual corticospinal integrity (do absent MEPs preclude benefit)? (3) Economic—does cost-effectiveness outperform botulinum toxin plus therapy in real-world settings (3, 29)? We are collaborating with a manufacturer on a dual-channel pTBS prototype, but the design metric isn't power output, but rather minimizing the “acoustic fingerprint” that undermines blinding. This engineering constraint may prove the study's most commercially relevant byproduct.

Ultimately, this RCT tests whether the W-shaped model's “optimal zone” exists at the individual level (28). Aggregated group means are secondary; single-subject excitability shifts determine the model's survival.

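### Three arms are compared by two-sample tests at an unadjusted 0.05 with no primary endpoint, so even one outcome at one visit carries about 9–12% false-positive risk instead of 5%

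*Protocol article*

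**What the plan says.** Study design describes three parallel arms, the last being "3) active iTBS+active cTBS in 1:1:1 ratio", assessed at baseline, after the 10 sessions (T1) and two weeks later (T2).

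Statistical analysis names the tests. Under normality, "repeated-measures analysis of variance will be used for intra-group comparisons and independent-samples *t*-test for inter-group comparisons". Where normality fails, the section turns to rank-based counterparts, of which the second again handles only two groups: "Friedman test and Wilcoxon rank-sum test will be adopted". It then sets one threshold: a p "value < 0.05 will be considered statistically significant". It mentions no adjustment, no testing order and no three-group test between arms.

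The target of the trial is described in several ways:

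- Introduction: "Primary objectives are to evaluate pTBS effects on spasticity/function, investigate neurophysiological mechanisms, and establish safety profiles".
- Abstract, anticipated results: Group 3 is expected to show the largest fall in MAS and the "most significant improvements in upper-limb function (FMA-UE, ARAT) compared to Groups 1 and 2".
- Sample size estimation: a pooled d of 0.60 for upper-limb motor improvement, converted to f of about 0.30 for three groups.

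Outcome measures lists three MEP metrics ("The following metrics will be obtained: (1) resting motor threshold (RMT", then amplitude and latency) and four scales: MAS, FMA-UE, ARAT and Modified Barthel Index.

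**The concern.** A t-test or rank-sum test handles two groups. With three arms, each between-group comparison therefore becomes up to three pairwise tests. Repeated-measures ANOVA and Friedman are reserved for change within groups, so nothing stands in front of the pairs. The nominal 5% is then exceeded on a single outcome, before several outcomes or visits are considered.

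The lack of a primary endpoint matters more than usual here. The Discussion reports pilot data in which cTBS alone lowered MAS without improving ARAT, and iTBS alone did the reverse. If the trial repeats that pattern, Group 3 could beat Group 1 on MAS and Group 2 on ARAT. Either result could be reported as superiority of dual-site stimulation, although Group 3 had not beaten both single-site arms on any one outcome. The article gives no rule for what counts as a positive trial.

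**Working it through.** **Inputs from the protocol article.** Three arms, so 3 pairs, of which 2 involve Group 3. Seven outcomes: RMT, MEP amplitude, MEP latency, MAS, FMA-UE, ARAT, Barthel. Two post-baseline visits. Threshold 0.05. Planned size 18 per arm recruited, 15 per arm (45 in total) completing. The article states no familywise error rate, so the nominal 5% is the figure to check.

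**Inputs assumed.** No true difference between any arms (the global null); normal data; correlations between outcomes and between visits, which the documents do not give and which are therefore varied.

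**Step 1: one outcome, one visit.** If tests were independent, the chance of at least one false positive in m tests would be 1 − 0.95^m.

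- Three pairs: 1 − 0.95³ = 14.3%.
- Two Group 3 contrasts: 1 − 0.95² = 9.8%.

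The pairs share arms, so the true values are a little lower. Simulation with 15 per arm gives about 12% and 9%, and 18 per arm gives the same. This step needs no assumption about outcome correlation or about how many outcomes are tested.

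**Step 2: all outcomes and visits, if tested the same way.**

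- All pairs: 3 × 7 × 2 = 42 tests; expected false positives 42 × 0.05 = 2.1.
- Group 3 contrasts only: 2 × 7 × 2 = 28 tests; expected 28 × 0.05 = 1.4.

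The independence formula gives 1 − 0.95^42 = 88.4% and 1 − 0.95^28 = 76.2%. These are upper figures. With the shared arms built in but outcomes and visits uncorrelated, the 42-test value is 84%. Simulated ranges (20,000 trials per setting, visit correlation 0.5 to 0.9) are:

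| Outcome correlation | 42 tests | 28 tests |
|---|---|---|
| 0.2 | 70–80% | 59–69% |
| 0.3 | 68–77% | 57–67% |
| 0.5 | 60–70% | 50–60% |
| 0.6 | 55–65% | 45–54% |
| 0.7 | 50–59% | 40–49% |
| 0.8 | 43–52% | 34–42% |
| 0.9 | 34–43% | 27–34% |

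**Step 3: smaller families.** With clinical scales correlated 0.5–0.8 among themselves and MEP measures 0.3–0.5, the four scales alone (3 × 4 × 2 = 24 tests) give 34–48%. The three MEP measures alone (3 × 3 × 2 = 18 tests) give 37–44%.

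**Step 4: the remedies, one outcome at one visit.**

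- Requiring Group 3 to beat both other arms at two-sided 0.05: about 0.5% false claims under the global null. If Group 3 equals one arm and is far better than the other, the rate is about 2.5%, the one-sided size of a single test.
- Pairwise tests only after a significant three-group F test: about 5% under the global null.

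**The case against.** The strongest reply is that the article does not say every pair is tested on every outcome at both visits. The opening sentence of Statistical analysis mentions only MEP data, and the stated hypothesis concerns two pairs. That stands: 42 is a ceiling inferred from the outcome list.

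A reader might go further and infer that a false-positive claim is more likely than not. The documents do not support this. It needs the global null, the full 42-test family, and outcome correlations below about 0.7–0.8. FMA-UE and ARAT both measure upper-limb motor function, so high correlation between them is plausible.

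A reader might also take the Discussion's remark that "Aggregated group means are secondary" as a competing primary endpoint. In context it concerns whether the W-shaped model's optimal zone exists in individuals, and it designates no trial endpoint.

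Sample size estimation uses a three-group f, which suggests an overall test was in mind. With exactly three groups, such a test followed by unadjusted pairs would hold the error near 5% per outcome. But Statistical analysis does not state that step and names two-sample tests in its place, so the two sections need reconciling.

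Finally, an article condenses the full protocol, and the trial claims only preliminary evidence. That excuses silence on adjustment for secondary outcomes. It does not excuse the present text, which fixes both the tests and the threshold; an analysis plan that follows it inherits the error.

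**Conclusion.** The point holds in this form. Followed as written, the plan does not keep its nominal 5% even for one outcome at one visit: the rate is about 12% over three pairs, or 9% over the two hypothesised contrasts. This rests only on the global null and approximately normal data.

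The wider figure is conditional. If all listed outcomes and visits are tested, the chance of at least one false positive is about 55–80% at outcome correlations of 0.2 to 0.6. It drops below 50% at about 0.8 or more, or at about 0.6–0.7 if only the Group 3 contrasts are tested.

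Naming a single endpoint would not cure the problem alone, because the 9–12% remains until the pairs are governed by a rule.

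**What to change.** Before unblinding:

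1. **Primary endpoint.** The investigators name one outcome and one visit. The choice is theirs, but it must be reconciled with two statements: Outcome measures treats a sustained fall in MAS as meaningful, which bears on the choice between T1 and T2, and Sample size estimation uses a motor effect size, not a spasticity one.
2. **Decision rule.** Limit confirmatory testing to Group 3 against Group 1 and Group 3 against Group 2. Claim dual-site superiority only if both are significant in favour of Group 3 at two-sided 0.05. This matches the hypothesis and needs no split of alpha. Alternatively, run pairwise tests only after a significant three-group test, which matches the f used for sizing.
3. **Secondary outcomes.** Test any key secondary outcomes only after the primary succeeds, by one named procedure: a fixed sequence or Holm, not a mixture.
4. **Everything else.** Report Group 1 against Group 2, MEP measures, Barthel and the remaining visit as exploratory, with confidence intervals.

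The text change is about a paragraph, but the cost in power should be stated openly. At d = 0.60, a single pair has 35% power with 15 per arm and 42% with 18. The both-contrasts rule succeeds about 20% and 25% of the time if d = 0.60 on both contrasts, and about 2% if one of them is null. The pilot pattern makes that last case possible: Groups 2 and 3 both receive active cTBS, so they may differ little on MAS. The three-group route is also weak: at f = 0.30, a one-way ANOVA with 45 participants has 39% power. In either case, fewer outcomes can carry a positive claim.
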